#### Enrollment

Patients with age above 40 who applied to family medicine units for any reason and screened within the scope of periodic health care for diabetes are eligible for the study. Guidelines determine that 40 is the age to start diabetes screening for people without having any risk factors [9, 10].

Around 3000 people over the age of 40 apply to the 10 family medicine units in Izmir, Turkey each month. At least 14% of these people (DM prevalence is accepted about 14%) are expected to be eligible for inclusion criteria. 3000 individuals will be evaluated in terms of inclusion and exclusion criteria. Thus, the expected sample size will be reached.

Excluded and refused to participate: Selected participants after being assessed for eligibility will be asked about voluntariness for intervention. They will be taken informed consent. Then the participants will be taken to randomization.

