#### Allocation

Eligible participants will be assigned to intervention and control groups with simple randomization using a computerized random number generator for assignment into two groups. 110 patients will be allocated to the intervention group and 329 patients to the control group. Three physicians will treat and monitor intervention group using the CDSMS. In the control group, seven physicians will treat and monitor without using CDSMS.

Researchers will determine the random allocation sequence and make lists of sequence. These lists will be given to the nurses of the family medicine center. The nurses will assess the patient according to eligibility criteria and allocate eligible patients to either intervention or control groups depending on the lists.

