### Procedure

#### Stage 1

In the first stage, understandability, usability and adequacy of CDSMS software will be tested. 5 physicians will test CDSMS on at least 16 diabetes patients. The system will be revised according to the comments received on the Web Site Usability Test [38] and feedback form.

#### Stage 2

At this stage, a randomized controlled trial will be performed. Firstly, the physicians who manage the treatment of the patients will register online through the web based portal for free. The researchers will train these physicians about the use of portal.

Patients who are referred to select family medicine centers for any reason will receive diabetes screening using CDSMS. The patients who were previously diagnosed as diabetics will be recruited for trial by the physicians. The recruited patients will register to the CDSMS via mobile phone or web page with the accounts provided by their physicians, free of charge.

The proposed clinical decision support system is a recommended tool for primary care physicians to make clinical decisions on screening, diagnosis, treatment and monitoring of DM patients. Physicians input the data of patients having FPG, HbA1c or PPG test results in last six months. CDSS will make a statement on diagnosis of patient and/or stage. The system will also suggest a treatment plan for the patient. The physician will evaluate the system’s recommendations and decide on a treatment for the patient and input his/her treatment decision. CDSS will suggest a monitoring plan to the physician. The physician will evaluate the proposals and input the monitoring plan that he/she has decided for the patient into the system. The follow-up visits will happen with the physician. There are two options for carrying out the monitoring process:

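### The nurses who assess eligibility also hold the allocation lists, and no step is described that hides the next assignment, so protection against selection bias is not assured

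*Protocol article*

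**What the plan says.** The procedure is in the Allocation section of the protocol article (Stage 2). On who makes and who holds the sequence: "Researchers will determine the random allocation sequence and make lists of sequence. These lists will be given to the nurses of the family medicine center". On who uses it: "The nurses will assess the patient according to eligibility criteria and allocate eligible patients to either intervention or control groups depending on the lists". The method is "simple randomization using a computerized random number generator for assignment into two groups", and the same section fixes the arm sizes: "110 patients will be allocated to the intervention group and 329 patients to the control group".

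Three other places bear on the point. The Enrollment section puts eligibility first, then willingness and consent, then randomisation: "Selected participants after being assessed for eligibility will be asked about voluntariness for intervention". The Procedure section (Stage 2) names a different gatekeeper: "The patients who were previously diagnosed as diabetics will be recruited for trial by the physicians". Design and settings describes the trial as single blind without saying who is blinded.

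**The concern.** Randomisation prevents selection bias only if whoever decides on a patient's entry cannot know which arm comes next. Here one role receives the sequence, judges eligibility and assigns the arm.

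There is room for that judgement to be influenced. Table 1 asks for computer and Internet literacy, excludes communication problems, and accepts diabetes symptoms as a diagnostic criterion. The Stage 2 text includes weakness and fatigue among those symptoms. The intervention relies on patients sending data through a mobile application or a transfer device, so staff may be inclined to keep digitally able, motivated patients for it. Such patients may do better over six months whatever the system contributes, and the difference would then be credited to the system.

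**Working it through.** **1. Is the next assignment hidden anywhere?**

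- *Allocation:* the lists go to the nurses, who assess eligibility and allocate from them. No sealed envelopes, central or web release, or separation of list holder from assessor is mentioned.
- *Enrollment:* consent precedes randomisation. That order conceals nothing from an assessor who already has the list.
- *Design and settings:* blinding concerns what is known after assignment. It does not supply concealment.
- *Simple randomisation:* the next assignment is unpredictable only to someone without the list.

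No section supplies the missing step.

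**2. The plan's sample size.** Inputs from Stage 2: alpha 0.05 (two-sided assumed, as the article does not say), 80% power, 25% controlled, odds ratio 2, ratio 1:3, 15% loss. An odds ratio of 2 on 25% gives odds 2 × 0.25/0.75 = 0.667, that is 40%. The article names no formula. Kelsey's formula, with k = 3, difference 0.15 and weighted mean proportion (0.40 + 3 × 0.25)/4 = 0.2875, gives

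n1 = (1.96 + 0.842)² × 0.2875 × 0.7125 × 4/(3 × 0.15²) = 95.28, and n2 = 3 × 95.28 = 285.83.

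Multiplying by 1.15 gives 109.6 and 328.7, rounded up to 110 and 329, total 439. The plan's figure is reproduced, and nothing in this point changes it.

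**3. Illustration of what steering could do.** Assume no true effect, 25% controlled in the control arm, and a two-sided 5% unadjusted test of proportions on 110 against 329. The size of the imbalance is an assumption; the article gives none. For a spurious 5 points (30% against 25%):

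- pooled proportion = (110 × 0.30 + 329 × 0.25)/439 = 0.2625
- standard error used by the test = √[0.2625 × 0.7375 × (1/110 + 1/329)] = 0.0485
- actual standard error = √[0.30 × 0.70/110 + 0.25 × 0.75/329] = 0.0498
- rejection rate = Φ[(0.05 − 1.96 × 0.0485)/0.0498] + Φ[(−0.05 − 1.96 × 0.0485)/0.0498] = 0.183 + 0.002 = 0.185

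With the null variance in both places (standard error 0.0477, shift 0.05/0.0477 = 1.05) the result is 0.182. Either way it is about 18%.

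| Assumed spurious difference | Rejection rate, 110 vs 329 | After 15% loss in each arm |
|---|---|---|
| 2.5 points | 9% | 8% |
| 5 points | 18% | 17% |
| 10 points | 53% | 47% |

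The last row is two thirds of the planned 15-point effect and marks an upper end, not an expectation. A larger sample would raise these rates.

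**4. Fixed counts under simple randomisation.** With 439 patients and probability 0.25, the expected intervention count is 109.75, with SD √(439 × 0.25 × 0.75) = 9.07. The 95% range is 92 to 128, and the chance of exactly 110 is 4.4%. The effect on precision is small. At 92 against 347 the standard error changes by the factor √[(1/92 + 1/347)/(1/110 + 1/329)] = 1.06. At 128 against 311 it falls.

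**The case against.** The strongest reply is that this is a condensed article and the full protocol may describe sealed lists. A reader might infer that the lists are open and that randomisation has failed. The text supports neither: it does not say the lists are unsealed, and it shows that steering is possible, not that it will occur. That limits the wording, but the point stands. The article does not merely leave concealment out. It states a procedure that joins list holding, eligibility assessment and allocation in one role.

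A reader might also infer that no analysis could help, or that 18% is the type I error of the main analysis. Neither follows. The Statistical analysis section plans a mixed model with a Group by Period interaction for the primary outcomes, so an imbalance in glycaemia at entry is measured and largely separated from the effect of interest. What remains is unmeasured motivation or digital ability, which can act on the change itself. The same section also plans t-tests at the end of the intervention, which adjust for neither. The 18% belongs to an unadjusted comparison with an assumed imbalance.

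Other parts of the reply are fair. Volunteering is the patient's own decision, so it is a weak example of a criterion that a nurse can bend. The nurses are also not the only gatekeepers, since physicians recruit. The count mismatch creates no bias, and 110 and 329 can be read as targets. Permuted blocks are not needed for concealment and make assignments easier to guess for staff who know past ones. Stratifying by centre may not fit a trial in which three physicians treat one arm and seven the other.

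**Conclusion.** The concern holds in a bounded form. As written, the Allocation section gives the sequence to the people who judge eligibility, and no other section hides the next assignment, so protection against selection bias is not assured. This should be settled before enrolment, because bias from unmeasured patient characteristics cannot be removed afterwards.

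The size cannot be derived from the article. On the stated assumptions, the false-positive rate of an unadjusted comparison is 9% to 53% for spurious differences of 2.5 to 10 points, and about 18% at 5 points. These figures show sensitivity and do not forecast what will happen.

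The mismatch between simple randomisation and exact arm sizes is a real but secondary inconsistency, with little effect on precision.

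**What to change.** Change the Allocation section so that:

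- the sequence is generated and held by someone who takes no part in recruitment or eligibility assessment;
- each assignment is released only after eligibility and consent are irrevocably recorded, either by a web release or by sequentially numbered sealed opaque envelopes;
- the respective roles of nurses and physicians in recruitment are reconciled with the Procedure section.

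A web release need not be part of the CDSMS. The article describes no randomisation function there, and control physicians work without the system.

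Secondarily, either state 110 and 329 as expected targets under simple 1:3 randomisation (95% range about 92 to 128 in the intervention arm), or name a restricted 1:3 method that delivers those counts.

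The cost is minor set-up work and a few sentences of protocol text. The sample size stays at 439.

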#### Follow-up

Patients in both groups will be followed up for 6 months. Data from 0th month and 6th month will be compared.

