• Over age 40 • Volunteer • Computer and Internet literacy • DM diagnosed or having at least one of diagnostic criteria. These criteria; • HbA1c ≥ 6.5 • FPG ≥ 126 mg / dl • 2-h postprandial glucose ≥200 mg / dl • Any time postprandial glucose ≥200 mg / dl • Diabetes symptoms	• Having communication problems • Type 1 diabetes • MODY type DM • Psychotic disorders • Dementia

### Stage 2

In the second stage, the health data of 3000 participants will be evaluated to determine the effectiveness of CDSMS in screening. Participants who use medicine for DM treatment will be excluded from data analysis when measuring the effectiveness of the system in screening.

Patients who applied to primary health care services for any reason and screened within the scope of periodic health care for diabetes, having at least one measurement of FPG (Fasting Plasma Glucose), HbA1C or PPG (Postprandial Plasma Glucose) in last six months will be participants of stage 2. Participants determined in second phase will be evaluated in terms of inclusion and exclusion criteria. Eligible and volunteer participants will take part in the trial. Inclusion and exclusion criteria for randomized controlled trial are listed below in Table 1.

Patients who were diagnosed with DM among 3000 participants (new diagnosis, former diagnosis, medicine users, non-medicine users) will form the population of the randomized controlled trial. The sample size evaluated by significance level *p* = 0.05, 80% power, 25% prevalence (controlled diabetes) and odds ratio 2 will be included to experimental study. Because in RCT studies lost to follow up is approximately 15.0%, this amount is taken into account for determining the sample size. The sample contains 439 patients with 110 interventions and 329 control groups. The ratio of intervention to non-intervention (controls) is 1:3. About 3000 people over age 40 apply to the 10 primary health care units (In the city of Izmir in Turkey) in a month. For reaching expected number of samples, at least %14 of patients are thought to be eligible for inclusion criteria. (assuming DM prevalence approximately 14%).

Diabetes symptoms aforementioned in Table 1 are classical symptoms of polyuria, polydipsia, polyphagia or loss of appetite, weakness, fatigue, dry mouth, nocturia. Less common symptoms are blurred vision, unexplained weight loss, persistent infections, recurrent yeast infections and itching [10].

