### Measures

Primary outcomes of RCT include HbA1c, Fasting Blood Glucose and Postprandial Blood Glucose levels. Secondary outcomes include body mass index, diabetes-related emotional burden and interpersonal distress sub-scales, self-efficacy for diabetes self-care, blood glucose monitoring, physical activity, nutrition, medication-taking, diabetes self-care: blood glucose self-monitoring, medication-taking, smoking and alcohol using and physical activity, depression, anxiety, stress levels. Clinical and laboratory outcomes will be face-to-face assessed, others will be online self-assessed. The effectiveness of the system will be evaluated by using primary and secondary outcomes.

Table 2 lists all the outcomes and measures used in this study. Fasting blood glucose, HbA1c and other tests according to patient history and physical examination will be determined and implemented for each patient taken into intervention and control groups. Body mass index of patients will be calculated. On baseline all scales will be implemented online such as Diabetes Distress Scale [40], Diabetes Self-Efficacy Scale [41], Diabetes Self-Care Activities Survey [42], Morisky Medication Adherence Scale [43], The Patient Assessment of Chronic Illness Care-Patient Form [44, 45]. Monthly average of FPG and PPG values of patients regularly taken from the tele-monitoring system will be evaluated. Glycosylated hemoglobin (HbA1c) test will be done quarterly.

**Table 2 Tab2:** Measures

Measurement area	Outcomes assessed	Measure/s
Demographics	Age, gender, nationality, country of birth, relationship status, employment status, health insurance	Short answer and multiple choice items
Laboratory	Glycosylated hemoglobin A1c (HbA1c) level Fasting And Postprandial Blood Glucose	Venous blood sample
Clinical	Height, Weight, Diabetes Symptoms, Risk Factors	Patient history and physical examination
Emotional/ Psychological	Depression, anxiety, stress levels Diabetes-related emotional burden and interpersonal distress sub-scales Self-efficacy for diabetes self-care: blood glucose monitoring, physical activity, nutrition, medication-taking	Diabetes Distress Scale [40] Diabetes Self-Efficacy Scale [41]
Behavioral	Physical activity Diabetes self-care – blood glucose self-monitoring, medication-taking, smoking and alcohol using and physical activity	Diabetes Self-Care Activities Survey [42] Morisky Medication Adherence Scale [43]

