### Statistical analysis

Statistical analysis will be performed using SPSS software. As stated in the method section, the system will be tested in two stages.

### Stage 1

For the first stage, the comments in the feedback forms will be used for revisions of program. Descriptive analyzes will be done for web site usability test results.

### Stage 2

At the end of the intervention, independent samples t-tests will be performed to measure the difference between the intervention and control groups. On both groups, one-sample t-test will be performed to measure the difference between baseline and post intervention in the same group.

Each of the dependent measures of primary outcomes will be analyzed using a generalized linear mixed model involving a single between Group factor (Treatment vs. Control), a single within Period factor (enrollment vs. end of 6 months), and interaction between Group and Period factor. Categorical data of both control and intervention groups will be analyzed together using logistic regression. The rates of controlled and uncontrolled diabetes patients will be determined.

An intention-to-treat analysis will be performed. The analysis will include all individuals’ data. In the analysis, patients will be compared regardless of patient compliance, crossover to other treatments, or withdrawal from the study.

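### The primary mixed model for HbA1c has two time points although the test is quarterly, so the month-3 value of patients lost later enters no stated analysis; a third level would remove a small possible bias

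*Protocol article*

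**What the plan says.** The Measures section of the protocol article names HbA1c among the primary outcomes and states: "Glycosylated hemoglobin (HbA1c) test will be done quarterly". In a six-month trial this implies a value at month 3.

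The Follow-up section states: "Data from 0th month and 6th month will be compared". The Stage 2 text under Statistical analysis gives the model for each primary outcome "a single within Period factor (enrollment vs. end of 6 months"), together with Group and the Group-by-Period interaction. The t-tests listed there compare the groups at the end of the intervention, or baseline with the end within a group. No stated analysis names a month-3 value.

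The same section promises an intention-to-treat analysis of all individuals, whether or not they withdraw. Under Participants and sample size, loss is expected: "Because in RCT studies lost to follow up is approximately 15.0%, this amount is taken into account for determining the sample size".

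**The concern.** The article does not leave the time structure of the primary model open. It sets the levels of Period, and that choice leaves out a measurement of a primary outcome that it plans to take. For a patient lost after month 3, the month-3 HbA1c is the only HbA1c on study treatment and the value closest in time to the missing one. The two-level model has no place for it, which sits badly with the promise to include everyone's data.

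At stake is the month-6 group difference. A likelihood model with baseline and month 6 allows for loss that depends on baseline. It does not allow for loss that depends on month-3 HbA1c beyond what baseline predicts. If that dependence, or the rate of loss, differs between the arms, some bias stays in the comparison. A difference between arms is conceivable: CDSMS patients enter measurements and receive alerts and reminders, while controls continue with their usual care.

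**Working it through.** **1. The plan's own sample size, to fix the scale.** The stated inputs are "80% power, 25% prevalence (controlled diabetes) and odds ratio 2", significance level 0.05 (taken as two-sided) and a 1:3 ratio.
- Control odds 0.25/0.75 = 1/3. Times 2 gives 2/3, so the intervention proportion is 0.40.
- Weighted mean proportion: (0.40 + 3 × 0.25)/4 = 0.2875.
- Kelsey formula: n = (1.960 + 0.842)² × 0.2875 × 0.7125 × (1 + 1/3) / 0.15² = 95.28 in the intervention arm.
- 95.28 × 1.15 = 109.57, rounded up to 110. 3 × 109.57 = 328.7, rounded up to 329. The total is 439.

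This reproduces the article: "The sample contains 439 patients with 110 interventions and 329 control groups". The present point does not change it.

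**2. How many patients are concerned.** 0.15 × 439 = 65.9, about 66. If loss is spread evenly over six months (an assumption), half of them, about 33, leave after month 3. In the CDSMS arm this is 0.075 × 110 = 8.25, about 8 patients.

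**3. Size of the bias.** The article gives no SD, correlations or loss mechanism for HbA1c. Assumed: SD 1.5; correlations for months 0–3 / 3–6 / 0–6 of 0.5/0.7/0.4, 0.7/0.8/0.6 or 0.8/0.9/0.75; 110 against 329 patients. Where loss after month 3 depends on month-3 HbA1c, its log-odds rise by 1 per SD. Two-period means likelihood estimation from months 0 and 6; three-period adds month 3.

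*Loss spread evenly* (7.5% at random before month 3, about 7.5% after it), no true effect, dependence in the CDSMS arm only:
- 3,000 trials per setting, two settings with correlations between 0.5 and 0.8: two-period bias -0.041 and -0.043; three-period 0.003 and 0.000. Standard errors were 0.175 against 0.172, and 0.161 against 0.159.
- A repeat with 4,000 trials for each of the three correlation sets: two-period bias -0.060, -0.043 and -0.034; three-period within 0.004 of zero. Standard errors were equal to within 0.001. With the same mechanism in both arms, both estimators were within 0.005 of zero.

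*All loss after month 3*, true difference -0.5, 400 trials per setting, ranges over the correlation sets:

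| Loss, CDSMS / control | Dependence on month 3 | Bias, completers only | Bias, two-period | Bias, three-period |
|---|---|---|---|---|
| 15% / 15% | same in both arms | about 0 | about 0 | about 0 |
| 15% / 15% | CDSMS arm only | -0.13 to -0.18 | -0.05 to -0.11 | about 0 |
| 20% / 13.3% | same in both arms | -0.07 to -0.09 | -0.04 to -0.05 | within 0.02 |
| 30% / 10% | CDSMS arm only | -0.27 to -0.35 | -0.13 to -0.22 | within 0.02 |

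Overall loss is 15% in every row (for example, 0.30 × 110 + 0.10 × 329 = 65.9). The last row is a stress case that nothing in the article suggests.

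**4. Against the noise.** 0.041/0.175 = 0.23 and 0.043/0.161 = 0.27, so the bias in the evenly spread case is about a quarter of one standard error.

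**The case against.** A comparison of baseline with the endpoint is a legitimate choice that matches the six-month target. Details of missing-data handling commonly sit in an analysis plan, which is not at hand, and the short Analysis section hints that data from patients who leave follow-up will be used. This stands as far as imputation and sensitivity analyses go. It does not cover the Period factor, whose levels the article itself fixes.

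Four stronger readings are tempting, and the documents do not support them.

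- *The bias cannot be corrected.* The two-period model, if it keeps patients with baseline only, already removes part of it. The month-3 value is still collected and could enter the model or an imputation. The accurate statement is that the stated analysis does not use it.
- *Unequal loss is likely because the rule for ending the intervention applies to one arm.* Under Procedure, that rule ends the intervention on hospitalisation, request or death. It does not end follow-up, and patients are to be compared regardless of compliance. Unequal burden makes a difference between arms possible; nothing in the article makes it probable.
- *A month-3 HbA1c certainly exists in both arms.* The quarterly sentence follows one on tele-monitoring data, and controls are to have no further intervention. The schedule, Table 3, is a figure not available for this review. A month-3 test in controls is probable but not certain.
- *Any loss that depends on month 3 biases the comparison.* With the same mechanism and the same rate in both arms, the bias of the group difference is near zero, even for completers only.

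**Conclusion.** The point holds as a modest improvement to a model that the article specifies. As written, the month-3 HbA1c of patients lost between months 3 and 6 enters no stated analysis, despite the promise to include all data and an expected loss of about 15%.

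The likely harm is small. It is about -0.04 to -0.05 HbA1c points under SD 1.5, 15% loss spread evenly and dependence on month-3 HbA1c in the CDSMS arm only; across the three assumed correlation sets the range is about -0.03 to -0.06. It rises to between -0.05 and -0.11 if all the loss falls after month 3, and is near zero if mechanism and rate are the same in both arms. The sign follows from the assumption that patients with high HbA1c leave; if those with low HbA1c left instead, it would reverse. The gain in precision is negligible (0 to 2% in the standard error), so it is no reason for the change. All these sizes rest on assumed figures.

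Month-3 data deal only with loss that observed values explain.

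**What to change.** For HbA1c, give Period three levels (0, 3 and 6 months) in the planned mixed model, keep the month-6 group difference as the effect, and include every patient with at least one value. State that the quarterly HbA1c is taken in both arms. Add a sensitivity analysis for loss that depends on the unobserved month-6 value.

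If the test is already planned in both arms, the cost is a line or two of text. The sample size and the quantity estimated do not change. If it is planned for the CDSMS arm only, there are two options. One is to use the month-3 value only where it is collected, for example as an imputation variable in that arm, which leaves the controls uncorrected. The other is to add one HbA1c test per control patient, at most 329 tests.
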